## Abstract

**Background:**

Cognitive behavioral therapy (CBT) and interpersonal therapy (IPT) are among the most well established therapies for the treatment of depression. However, some major questions remain unanswered. First, it is unknown what session frequency results in the most optimal (cost) effectiveness in psychotherapy. Second, the debate as to what mechanisms underlie the effect of psychotherapy has not yet been resolved. Enhancing knowledge about the optimal session frequency and mechanisms of change seems crucial in order to optimize the (cost) effectiveness of psychotherapy for depression. This study aims to compare treatment outcome of twice-weekly versus once-weekly sessions of CBT and IPT. We expect twice-weekly sessions to be more effective and lead to more rapid recovery of depressive symptoms in comparison to once-weekly sessions. Both therapy-specific and non-specific process measures will be included to unravel the mechanisms of change in psychotherapy for depression. Besides the use of self-reports and behavioral observations, this study will also examine underlying biological processes by collecting blood samples.

**Method:**

In a multicenter randomized trial, two hundred depressed patients will be recruited from Dutch specialized mental healthcare centers and randomized into one of the following groups, all receiving a maximum of 20 sessions in different frequencies: a) twice-weekly sessions at the start of CBT, b) twice-weekly sessions at the start of IPT, c) once-weekly sessions at the start of CBT, d) once-weekly sessions at the start of IPT. Primary outcome measures are depression severity, cost-effectiveness and quality of life. Process measures include therapeutic alliance, recall, therapy-specific skills, motivation and compliance. Assessments will take place during baseline, monthly during treatment and follow-up at month 9, 12 and 24. In addition, at 12 and 24 months, the frequency of depressive episodes in the previous year will be assessed. Blood samples will be taken pre- and post-treatment. The study has been ethically approved and registered.

**Discussion:**

Finding that twice-weekly sessions are more effective or lead to more rapid recovery of depressive symptoms could lead to treatment adaptations that have the potential to reduce the personal and societal burden of depression. In addition, insight into the mechanisms of change and physiological processes in psychotherapy will enable us to optimize treatments and may help to understand human functioning beyond the context of treatment.

**Trial registration:**

The study has been registered on October 21th, 2014 at the Netherlands Trial Register, part of the Dutch Cochrane Centre (NTR4856).

## Background

Cognitive (behavioral) therapy (CBT) [1] and interpersonal therapy (IPT) [2] are among the most well established short-term therapies for the treatment of depression. Both treatments are effective and are recommended as first-choice treatments [3–6]. However, despite the efficacy and the acceptance of these therapies among researchers and clinicians, some major questions remain unanswered. This study will address two questions about the effectiveness and change mechanisms of psychotherapy for depression. First, there is a lack of clarity about the optimal intensity of psychotherapy [7]. It seems important to know what session frequency will provide the most optimal (cost) effectiveness in psychotherapy as this could lead to more rapid recovery and a reduction of direct (e.g. health care) and indirect costs (e.g. fewer work-days lost). Second, there are still many uncertainties regarding how the psychotherapies actually work. Despite the numerous efforts to understand the change mechanisms in psychotherapy, this topic remains largely unresolved [8–13]. It is not clear if and to what extent therapy- specific elements (e.g. cognitive skills in CBT or relational skills in IPT), non-specific elements (e.g. therapeutic alliance), or both, contribute to the effects of psychotherapy. Moreover, there is an ongoing discussion about what methods are necessary to conduct a successful study on the mechanisms of change in psychotherapy [14]. However, when investigating mechanisms of change during psychotherapy it seems important to not only include patient self-report measures, but to investigate multiple layers of behavior (e.g. independent raters, biological measurements) [15]. This study aims to compare treatment outcomes of twice-weekly versus once-weekly sessions of two widely used types of psychotherapy: CBT and IPT. Both therapy- specific and non-specific process measures will be included to enhance clarity about the mechanisms of change in psychotherapy for depression. In addition, we will collect blood samples in order to investigate the (predictive) role of several physiological processes (e.g. oxytocin, brain-derived neurotrophic factor, DNA methylation and RNA markers) during the course of psychotherapy for depression. The main research questions are:What is the (cost) effectiveness of twice-weekly sessions versus once-weekly sessions at the start of psychotherapy for major depression (CBT or IPT) over the course of 24 months?What change mechanisms may be involved in mediating the effects of psychotherapy?

### Frequency of psychotherapy

Several studies have shown an association between the frequency of therapy sessions and symptom improvement [16–18]. More specifically, a recent meta-regression found a strong and positive association between the number of sessions per week and the effect size of psychotherapy for adult depression. In that study it was session frequency, in contrast to the total number of sessions, which was related to treatment outcome [7]. In routine mental health care, therapy sessions are commonly planned once a week. The original CBT manual by Beck does recommend two sessions a week in the beginning of therapy [1]. Most empirical trials (mostly from the US) have established that CBT is efficacious providing twice-weekly treatment [19, 20]. However, Beck’s guidelines have not been followed consistently and Dutch mental health guidelines do not even give an indication of the frequency of psychotherapy for depression [6]. Given this gap between recommended and actual practice, it seems important to investigate whether a higher intensity of treatment will lead to better and more rapid treatment outcomes and is related to lower rates of relapse. The question is whether the results of the controlled clinical trials can generalize to clinical practice when an empirically-supported treatment is not implemented in the manner in which it was done. Although both conditions will have the same maximum number of sessions, it is conceivable that patients in the twice-weekly condition will respond more quickly and need fewer sessions than patients in the once-weekly condition. This could lead to a reduction of both direct (e.g. health care) and indirect costs (e.g. fewer work-days lost). In addition, differences in treatment intensity might not only lead to differences in the length of treatment, number of sessions and a reduction of costs but also to the activation of different components of therapy within different phases of the treatment. It is possible that some components of therapy will become more effective or present when patients receive sessions twice a week instead of once a week. Furthermore, it will be interesting to see whether therapy type (CBT vs IPT) moderates the effect of initial session frequency (twice-weekly versus once-weekly). This study will be the first in the field of depression that directly tests the hypothesis that twice-weekly sessions lead to better outcomes than once-weekly sessions. If we find twice-weekly sessions to be more effective or to lead to more rapid recovery, this could lead to treatment adaptations that have the potential to reduce the societal burden of depression. In addition, the question why a particular session frequency is more effective than the other might lead to new directions for understanding change mechanisms in psychotherapy.

### Mechanisms of change

Nowadays, a broad range of therapies is available for the treatment of depression. Research points to the equal effectiveness of different psychotherapies (on average) and the number of effective psychotherapies seems to be even expanding [3, 21]. The fact that different psychotherapies stemming from different theoretical backgrounds seem to produce comparable outcomes (on average) raises the question as to whether the different treatments might work through common non-specific factors (e.g. therapeutic alliance) instead of the therapy-specific techniques (e.g. change in cognitive skills for CBT or relational skills for IPT) that are assumed to underlie the effects of a specific psychotherapies. However, after thirty years of meta- analyses that tried to support the notion that treatment efficacy is due to non-specific factors, the controversy remains [9, 12]. Critics point to the limitations of a design that includes pre- and post- assessments only, as if often the case in randomized controlled trials. Several methodological recommendations have been made to improve the quality research on change mechanisms in psychotherapy. First, mediators have to be monitored across the course of treatment and not only before and after [10]. The timing of these assessments is critical: change in the mediator must occur before change in the outcome in order to rule out reverse causality. To ensure that the change observed in the mediator was not the result of a causal path from early change in the outcome variable to subsequent change in the mediator, the measurement of the outcome measures should parallel the assessments of the change mechanisms [11, 13, 22]. Second, the inclusion of moderators into the research design could lead to new hypotheses about potential mediators [13, 22]. Third, studies should make use of more advanced statistical techniques that are capable of detecting causal mediation. An example includes growth mixture modeling [10]. This study will include both potential therapy-specific and non-specific mechanisms of change. These mechanisms will be measured after the first two weeks of treatment and once a month along with the outcome measures. We will include moderators that are expected to influence the direction or strength of the relation between the intervention and outcome. Furthermore, in order to analyze the mechanisms of change we will use a combination of structural equation modeling (SEM) and multilevel modeling [23]. In this way, we hope to provide the optimal conditions for detecting mechanisms of change in psychotherapy for depression within a multicenter randomized trial.

In this study, we hypothesize two pathways of change to be involved in the course of psychotherapy for depression (Fig. 1). First, we expect that a higher session frequency will enhance the quality of the relationship between patient and therapist. This relationship has been referred to as therapeutic alliance and involves the behaviors and processes within the session, patients’ and therapists’ objectives about therapy and the interpersonal attachment of mutual trust, confidence and acceptance. Previously, therapeutic alliance has been positively related to treatment outcome [24–26] while lower therapeutic alliance was associated with dropout [27]. Possibly, the relationship between patient and therapist will develop more rapidly when the contact is more intense. We expect that a better therapeutic alliance will lead to more patient motivation and compliance, as the therapist will have better opportunities to detect patient’s struggles in motivation and compliance. Subsequently, higher rates of motivation and compliance are expected to lead to better and faster treatment outcomes. The second pathway of change focuses on the process of learning. It is possible that a higher session frequency will increase patients’ learning processes resulting in better treatment outcomes. This seems congruent with previous studies that show that it is the survival of neurons born in the last five days that is important for learning [28]. Possibly, a higher frequency will increase the survival of neurons that are important for learning and as a consequence optimize learning processes. In this study, we will measure the degree the patient is able to recall the content of the previous session and the therapeutic-specific skills of the patient (e.g. cognitive therapy skills or interpersonal therapy skills). We expect that a higher session frequency will lead to better session recall that, as a consequence, will lead to the development of better therapy- specific skills. Better therapy-specific skills are expected to lead to better and faster treatment outcomes.

**Fig. 1 Fig1:**
[figure not shown]
Hypothesized pathways of change in psychotherapy for depression

### Physiological pathways in the course of psychotherapy for depression

In addition to the focus on self-reports or behavioral observations for detecting mechanisms of change, this study also aims to focus on deeper layers of behavior. Earlier studies showed that a variety of physiological levels are deregulated in depressed patients and can be restored with use of antidepressants [29–36]. In this study we will investigate the role of the brain-derived neurotrophic factor (BDNF) [30–32], methylation profile of the BDNF gene (e.g. CpG I and IV) [33, 34] and oxytocin [35, 36] and RNA marker profiles [37] during psychotherapy for depression. We expect levels of BDNF and oxytocin to restore during treatment (potential mediators) while the methylation profile of the BDNF gene (e.g. CpG I and IV) and RNA marker profiles might play a role in the prediction of treatment outcome (prognostic indices) and quite possibly differential treatment outcome (potential moderators).

## Method

### Design of the study

We will conduct a multicenter randomized trial with four parallel groups: a) twice-weekly sessions at the start of CBT (*n* = 50), b) twice-weekly sessions at the start of IPT (*n* = 50), c) once-weekly sessions at the start of CBT (*n* = 50), d) once-weekly sessions at the start of IPT (*n* = 50). The anticipated flow of subject enrolment is graphically shown in Fig. 2. In essence, this is a 2 × 2 factorial design that allows the comparison of frequency type (i.e. twice-weekly vs once-weekly) in the combined psychotherapy groups (i.e. CBT and IPT) and vice versa. The Medical Ethics Committee of VU University Amsterdam approved the study protocol (registration number 2014.337). The study is registered at the Netherlands Trial Register, part of the Dutch Cochrane Centre (NTR4856).

**Fig. 2 Fig2:**
[figure not shown]
Flow of participants

### Participants

We aim to include 200 patients that satisfy the following criteria: a. DSM-IV or DSM-V diagnosis of a major depressive disorder (MDD) (including chronic depression) or DSM-V diagnosis of a persistent depressive disorder, b. age > 18 c. the patient is currently not using antidepressants or the use of antidepressants has been unchanged for at least three months before start of treatment and no change in the use of antidepressants is planned, d. sufficient knowledge of the Dutch language, f. score > 19 on Beck’s Depression Inventory II (BDI-II) [37–39]. Patients will be excluded when a. there is a high risk of suicide according to the intake staff, b. they are diagnosed with drug or alcohol dependence, c. they have a primary diagnosis other than MDD, d. they are diagnosed (or suspected) with a cluster A or B personality disorder during the intake staff, e. they had psychotherapy (CBT or IPT) focusing on a major depressive disorder in the previous year or f. they have no access to internet facilities. The presence of a depressive disorder will be indicated by a diagnosis following the Structural Clinical Interview for DSM-IV Axis I disorders (SCID-I) [40] or Mini International Neuropsychiatric Interview Plus (MINI-Plus) [41].

### Sample size

Based on the meta-analysis of treatment intensity [7], we estimate the post-treatment effect size for the difference in depressive symptoms (BDI-II) between the main conditions (twice- versus once-weekly in the combined psychotherapy groups) to be 0.45. Based on this effect size (alpha = 0.05, power (1-ß) = 0.80, two-tailed), we need 79 participants per group (e.g. once versus twice-weekly sessions). Taking 25 % dropout into account, this means in total at least 200 depressed patients. The sample size should also suffice to detect possible interactions of a comparable effect size between treatment conditions.

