### Data-analyses: primary outcome measures

Acute and long-term effects of the interventions (respectively 6 and 12 months) will be analyzed using mixed regression. This will enable us to use all outcome ratings and fit the growth curve of time, enter separate levels for study therapists and clinical sites, and also deal effectively with missing values. Time to recovery and relapse (episode of MDD after remission) and recurrence (episode of MDD after recovery) in the course of follow-up (12 and 24 months) will be analyzed with Cox regression. In addition, we will determine the proportion of patients that show reliable and clinically significant improvement on the outcome measures. Our calculations will be based on the method of Jacobson and Truax [75] which prescribes that Clinical Improvement (CI) is based on both Reliable Change (RC), the extent to which the pre-to-post-difference score is reliable; and on Clinical Significant change (CSC), the extent to which post-treatment scores are clinically meaningful [76]. Although the major question of this study focuses on the intensity of psychotherapy for depression, this study will additionally explore whether the effect of treatment intensity differs between IPT and CBT by testing an interaction between treatment conditions.

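### Keeping 158 evaluable patients after 25% dropout takes 211 randomised, not 200: a minor arithmetic error worth about 2 points of power in the simple two-group calculation

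*Protocol article*

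**What the plan says.** The Sample size section of the protocol article gives the whole calculation. The effect size on the BDI-II after treatment is taken as a standardised difference ("twice- versus once-weekly in the combined psychotherapy groups) to be 0.45"), with "alpha = 0.05, power (1-ß) = 0.80, two-tailed". From this the text concludes "we need 79 participants per group", where a group is one of the two session frequencies with CBT and IPT pooled. It then takes 25% "dropout into account, this means in total at least 200 depressed patients".

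The same total appears elsewhere. The Participants section states "We aim to include 200 patients that satisfy the following criteria". The Design of the study section allocates 50 patients to each of four arms and describes the structure: "In essence, this is a 2 × 2 factorial design that allows the comparison of frequency type". The frequency comparison is therefore 100 against 100.

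On the analysis, the section on primary outcome measures plans a mixed regression and says of it: "This will enable us to use all outcome ratings and fit the growth curve of time". That section also says that the model handles missing values and carries separate levels for therapists and clinical sites.

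**The concern.** An allowance for dropout should ensure that the required number remains after the expected loss. Here it does not: taking 25% from 200 leaves 150, and the preceding sentence asks for 158. The text presents 200 as a minimum that satisfies its own inputs, and the other sections fix 200 as the target, so the words *at least* do not close the gap.

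What is at stake is the combination of power, effect size and dropout that readers will cite as the justification for the trial's size. The 79 per group has almost no slack, since 78 per group would already fall just under 80%. Any shortfall against 79 therefore takes the calculation below its stated level, though here only slightly.

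**Working it through.** **Inputs**, all from the Sample size and Design of the study sections: standardised difference d = 0.45; two-sided alpha 0.05; power 0.80; two groups of equal size; dropout 25%; total 200, which is 4 × 50 and so 100 per frequency group.

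**Step 1. Reproduce the 79 per group.** The normal approximation gives n = 2(1.960 + 0.842)²/0.45² = 77.5, so 78 per group. The two-sample t-test gives 78.49, so 79 per group, with power 80.3% at 79 and 79.7% at 78. The plan's 79 is the t-test answer and is correct. The evaluable total is 2 × 79 = 158.

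**Step 2. Inflate for dropout.** If a fraction w is lost, the number to randomise is N = n/(1 − w).

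- 158/(1 − 0.25) = 158/0.75 = 210.7, so 211.
- Per group, 79/0.75 = 105.3, so 106, or 212 with equal groups.

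The stated 200 is 11 to 12 patients short, or about 5% (11/211). For comparison, 158 × 1.25 = 197.5, which rounds up conveniently to 200.

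**Step 3. What 200 leaves.** 200 × 0.75 = 150, or 75 per group. That is 4 per group and 8 in total below the plan's own requirement.

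**Step 4. Consequence in the same two-group calculation.**

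| Evaluable per group | Power at d = 0.45, t-test | Power at d = 0.45, normal approximation |
|---|---|---|
| 79 | 80.3% | 80.7% |
| 75 | 78.2% | 78.7% |

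Against the stated 80%, the shortfall is 1.3 to 1.8 percentage points. With 75 per group, the t-test reaches 80% power at d = 0.460.

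**Step 5. Dropout that 200 can absorb.** 1 − 158/200 = 0.21. Up to 21% dropout, spread evenly over the groups, leaves the required 79 per group.

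**Step 6. Sensitivity to a baseline covariate (assumed correlation).** If baseline BDI-II were a covariate correlated rho with the outcome, the effective difference would be 0.45/√(1 − rho²). The document gives no value for rho. At 75 per group:

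| Assumed rho | Effective d | Power, t-test |
|---|---|---|
| 0.3 | 0.472 | 81.9% |
| 0.4 | 0.491 | 84.8% |
| 0.5 | 0.520 | 88.5% |

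**The case against.** The strongest reply accepts the arithmetic and disputes its weight. The loss is under 2 points of power, and the detectable difference moves from 0.45 to 0.46. The 0.45 is itself an estimate taken from a meta-analysis, so a shift of 0.01 has no practical importance. That stands, and it is why the point is minor.

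Three stronger readings are tempting, and the document does not support them.

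- A reader might infer that the trial will not have 80% power. The 78% belongs to a t-test in completers at one time point. The planned analysis is by intention to treat, with a mixed regression on a BDI-II measured at baseline, monthly to month 6 and then at follow-up, so patients who leave still contribute their earlier ratings. Nor does the text say whether dropout means leaving treatment or leaving assessment. Power under that model could be higher, through repeated measures or a baseline covariate, or lower, through the therapist and site levels. The document does not settle which.
- A reader might infer that the authors multiplied by 1.25. The figure fits, but no formula is shown, so the total is only consistent with that route. The error is the same by any route.
- A reader might infer that 80% power is wrong as stated. It is correct for 79 per group. The fault lies only in the conversion to a total.

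One part of the reply does not stand: the mixed model cannot be used to justify 200 as written. The Sample size section does not invoke it. The section takes a plain 25% allowance from a two-group calculation, and on those terms the total is wrong.

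**Conclusion.** The sentence is wrong as written, and the error is minor. On the plan's own inputs the total is 211 (212 for equal groups), not 200. With 200 randomised and 25% lost, 75 per group remain, and the two-group comparison in completers has about 78% power at d = 0.45, or 80% at d = 0.46.

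This rests on a t-test at a single time point, dropout spread evenly over the two frequency groups, and no information from patients who drop out. It says nothing about power under the planned mixed regression, and it is no ground for calling the trial materially underpowered or for requiring more patients. No part of the design, randomisation or analysis depends on the correction.

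**What to change.** Keep 200 patients and replace the dropout sentence with wording such as: *With 200 patients randomised, 25% dropout leaves 75 per frequency group, which gives about 78% power for a standardised difference of 0.45 in a two-sample t-test among completers; 80% power is kept if dropout does not exceed 21%.* The alternative is to state 211 (212 for equal groups) as the total, which would mean recruiting 11 to 12 more patients for a gain of about 2 points.

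If the sponsor prefers to quote power for a baseline-adjusted model, the text should name the assumed correlation and say that it is an assumption. At 75 per group the range is 81.9% to 88.5% for correlations of 0.3 to 0.5.

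The first option costs one sentence and lowers the stated power by about 2 points. It needs no change to recruitment.

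### The sample sized for a 0.45 SD main effect of session frequency does not also suffice for a 0.45 SD frequency-by-therapy interaction: on the same unadjusted basis its power is about 28–29% after dropout

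*Protocol article*

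**What the plan says.** Under Sample size, the protocol article takes the effect of interest to be the post-treatment BDI-II difference between the two frequencies, "twice- versus once-weekly in the combined psychotherapy groups) to be 0.45". The design values are "alpha = 0.05, power (1-ß) = 0.80, two-tailed", and the result is that "we need 79 participants per group (e.g. once versus twice-weekly sessions"). Dropout is then added: "Taking 25 % dropout into account, this means in total at least 200 depressed patients". The paragraph closes with "The sample size should also suffice to detect possible interactions of a comparable effect size between treatment conditions". No separate calculation is given for the interaction.

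Under Design of the study, the layout is four groups of 50: "In essence, this is a 2 × 2 factorial design that allows the comparison of frequency type" with CBT and IPT combined, and the reverse. Under Data-analyses: primary outcome measures, the interaction appears as a secondary matter: "this study will additionally explore whether the effect of treatment intensity differs between IPT and CBT by testing an interaction between treatment conditions".

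**The concern.** The closing sentence carries the main-effect calculation over to the interaction. The two contrasts are not estimated with equal precision. The main effect compares two halves of the sample. The interaction is the difference between two such comparisons, each made in only half the patients. A sample that just reaches 80% power for a main effect of 0.45 SD cannot come near it for an interaction of 0.45 SD.

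What is at stake is how the interaction result will be understood. The Background asks whether therapy type moderates the frequency effect, and the Discussion presents the trial as an opportunity to compare CBT and IPT in this respect. The main result also pools the two therapies. With a statement of adequate sample size on record, a non-significant interaction could be given more weight than the data can bear.

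**Working it through.** **Inputs (protocol article, Sample size and Design of the study).** Effect size 0.45, taken with SD = 1; two-sided alpha 0.05; power 0.80; 79 per frequency group, so 158 in total; 25% dropout; 200 randomised in four equal cells of 50. If 25% of 200 are lost, 200 × 0.75 = 150 remain, so both 150 and 158 are shown below.

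**1. Reproduce the stated figure.** By the normal approximation, n per group = 2 × (1.96 + 0.8416)² / 0.45² = 77.5, rounded up to 78. The two-sample t-test gives 78.49, rounded up to 79, with power 80.3% at 79 per group. The stated 79 reproduces as an unadjusted two-group comparison.

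**2. Standard errors with N analysed, N/4 per cell, in SD units.**
- Main effect of frequency: SE = √(4/N).
- Interaction (frequency effect in CBT minus frequency effect in IPT): SE = √(16/N), exactly twice as large.

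**3. Power for an interaction of 0.45 SD**, as Φ(0.45/SE − 1.96), with a noncentral t check on N − 4 degrees of freedom:

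| N analysed | SE of interaction | 0.45/SE | Power (normal) | Power (t) |
|---|---|---|---|---|
| 150 | 0.327 | 1.378 | 28.0% | 27.8% |
| 158 | 0.318 | 1.414 | 29.3% | 29.0% |
| 200 | 0.283 | 1.591 | 35.6% | 35.3% |

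**4. Smallest interaction detectable with 80% power**, (1.96 + 0.8416) × √(16/N): 0.91 SD at N = 150, 0.89 SD at N = 158, 0.79 SD at N = 200.

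**5. Sample needed for 80% power at 0.45 SD:** 16 × (1.96 + 0.8416)² / 0.45² ≈ 620 analysed, or 620/0.75 ≈ 827 randomised. This shows the scale of the gap; it is not a recommendation.

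**6. The alternative reading, equal Cohen's f.** A main effect of 0.45 SD corresponds to f = 0.45/2 = 0.225. An interaction with f = 0.225 is a difference between the two frequency effects of 4 × 0.225 = 0.90 SD. With an average effect of 0.45, that means 0.90 in one therapy and 0.00 in the other. Power is then 78.7% at N = 150, 80.7% at 158 and 88.9% at 200 (t-based: 78.2%, 80.2%, 88.6%). By contrast, an interaction of 0.45 SD around the same average would be effects of 0.675 and 0.225.

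**7. Sensitivity to a more efficient analysis.** The documents give no baseline or repeated-measures correlation r. Assuming r between 0.3 and 0.7, and dividing 0.45 by √(1 − r²), the t-based power is 30–50% at 150–158 and 38–60% at 200. Reaching 80% would require √(1 − r²) = 0.45/0.8915 at N = 158, so r ≈ 0.86, or 0.45/0.7924 at N = 200, so r ≈ 0.82.

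**The case against.** The best defence is that the sentence never defines the size of the interaction. In analysis-of-variance terms, comparable can mean equal f, and on that reading power at 158 is almost exactly the design power. That shows the sentence can be rescued, but not that it says this. The article never uses f, and it expresses its effect size as a difference of 0.45. A gap of 0.90 SD, with all the benefit in one therapy, is not what a reader would take as comparable to 0.45.

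A second defence is that the planned analysis is an intention-to-treat mixed regression using all outcome ratings, so 28–29% is close to a floor. This stands in part: the figure belongs to an unadjusted comparison of the patients left after dropout. But the closing sentence rests on that same unadjusted calculation, and the assumed correlations of 0.3 to 0.7 do not bring power to 80%.

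A third defence concerns weight, and it stands. The two main research questions in the Background do not include moderation by therapy type, and the analysis section sets the interaction apart as something to explore.

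A reader might also infer three stronger things. One is that the protocol states 80% power for the interaction; it does not, and that level is only implied by placing the claim directly after the 80% calculation. Another is that a null interaction will be reported as equal effects in CBT and IPT; no section says so. The third is that the pooled frequency comparison is compromised; nothing makes it depend on the interaction test.

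**Conclusion.** On its plain reading, the statement that the sample suffices for a comparable interaction is wrong. On the protocol's own unadjusted basis (two-sided 0.05, equal cells, effect 0.45 SD), the test would miss such an interaction about 7 times in 10 after dropout (1 − 0.28 = 0.72 at N = 150), and about 64% of the time with all 200 analysed. The sentence is correct only for a gap of about 0.90 SD.

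The conclusion assumes that comparable refers to the quoted difference of 0.45. The exact power depends on how many patients are analysed and on a correlation that the documents do not give; the conclusion that power falls well short of 80% does not change over the range tried. The test is exploratory and the primary comparison is untouched, so this should be fixed but does not threaten the trial's main result.

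**What to change.** Replace the closing sentence of the Sample size section with wording such as:

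> The trial is sized for the main effect of frequency. On the same unadjusted basis, power for a 0.45 SD frequency-by-therapy interaction is about 28–29% after 25% dropout (about 36% with no loss), and 80% power is reached only for a difference of about 0.9 SD (about 0.8 SD with no loss). The interaction is exploratory and will be reported as an estimate with a 95% CI; a non-significant result will not be taken as evidence of equal effects.

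The cost is one sentence of wording and a less favourable statement of what the trial can show. Do not enrol more patients on this account; the design and the primary analysis stay as they are. The article describes recruitment as ongoing, so the correction can be made before results are known.
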